### Selection of the “e-Cigarette Case” Group

#### Inclusion Criteria

A prospective study among experimental participants who smoked e-cigarettes over the last 210 days or 7 months will be conducted. According to the article “Effects of Duration of Electronic Cigarette Use,” the average duration of use among e-cigarette smokers is 210 days or 6.8 months [15]. The same criteria will be used in this study to standardize the duration of use for both the conventional cigarette smoking population and the e-cigarette smoking population.

#### Exclusion Criterion

The exclusion criterion is participants who smoke tobacco.

### Selection of Controls

Inclusion criteria are individuals without a history of smoking e-cigarettes, drinking alcohol, and smoking tobacco at the time of recruitment.

Exclusion criteria are participants who smoke e-cigarettes and tobacco.

### Recruitment Strategy

#### Overview

The recruitment strategy, targeting customers at e-cigarette stores and pedestrians, is strategically aligned with the study’s focus on e-cigarette users. The inclusion of community selection for matching controls, if quotas are not met, demonstrates flexibility in the recruitment approach. The disclosure of convenience and nonprobability sampling methods ensures transparency, thereby acknowledging the limitations inherent in these methods. A nuanced understanding of participant selection challenges is crucial for the accurate interpretation of study findings.

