#### Community Selection Details

If quotas for controls are not met through the initial recruitment strategy, a community selection approach will be considered. This involves identifying and recruiting controls from community settings, ensuring a diverse representation.

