### Clinical Recruitment Procedures

#### e-Cigarette Store Recruitment

The e-cigarette store recruitment consists of 3 stages, which are as follows:

Approach: e-cigarette stores will be approached to seek their cooperation in the recruitment process.Informed consent: store owners and managers will be provided with detailed information about the study objectives, procedures, and ethical considerations. Upon agreement, consent forms may be obtained from the store owners to allow recruitment on their premises.Participant identification: e-cigarette users within the specified age range will be approached, and the study will be explained to them. Interested individuals will be given detailed information about the study and their consent will be sought.

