#### Pedestrian Recruitment

The pedestrian recruitment consists of 2 stages, which are as follows:

Approach: pedestrians in high-traffic areas will be approached with an invitation to participate in the study.Informed consent: similar to the e-cigarette store recruitment, detailed information will be provided to potential participants, and consent will be obtained before proceeding with any study-related activities.

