#### Community Selection (if Necessary)

If quotas for controls are not met through the initial recruitment strategy, community selection may be considered.

Approach: community settings such as local community centers or public spaces will be identified. Consent from relevant authorities and community leaders will be sought.Participant identification: controls meeting the study criteria will be approached in these settings, and recruitment will follow the same informed consent procedures.

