### Sampling Methods

Convenience and nonprobability sampling methods will be used for the recruitment of cases and controls. The detailed sample size determination is shown in Multimedia Appendix 1 [16]. Briefly, the predefined power is 80% (*P*=.04), and the predefined proportions of the case and controlled groups are 11% and 2.5%, respectively. In all, 304 youths aged 15 to 24 years (n=152, 50% who smoke only e-cigarettes and n=152, 50% who do not smoke e-cigarettes or cigarettes) will be recruited.

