### Data Collection: Questionnaire

Interviewer-administered questionnaires will be used to collect data on demographic, lifestyle, and socioeconomic variables for the cases and controls. The questionnaire tool will comprise 2 parts: exposure information (part A) and sociodemographic information (part B). A life grid sheet will be used during interviews to efficiently collect retrospective information on lifestyle habits and other risk factors. To reduce observer bias, interviewers will not initially be informed about the aim of the research. Once cases are identified and interviewed, matching controls will be recruited and interviewed. Answers provided by participants will be converted to objective scores after data collection by the investigator (SC). The details on the parts of the questionnaire are as follows.

Exposure information (part A) will include (1) oral mucosal health status (whether white spots are present), (2) smoking habits, (3) type of products used, (4) e-cigarette smoking status (yes or no and current or previous), (5) age of onset, (6) duration of smoking, (7) pattern of smoking duration (continuous or intermittent), (8) frequency of smoking (daily, weekly, and occasionally), (9) number of cartridges (frequency), and (10) Tobacco consumption. Sociodemographic information (part B) will include (1) age, (2) sex, (3) occupation type, (4) education level, (5) income, and (6) ethnicity.

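### Stores supply only e-cigarette users and the community top-up only controls, so recruitment source is partly tied to exposure and nothing stated offsets it

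*Protocol article*

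**What the plan says.** The Recruitment Strategy overview names two initial sources, "targeting customers at e-cigarette stores and pedestrians". The later sections say who is approached in each:

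- **Stores** (e-Cigarette Store Recruitment): "e-cigarette users within the specified age range will be approached, and the study will be explained to them". Nobody else is approached there.
- **Street** (Pedestrian Recruitment): "pedestrians in high-traffic areas will be approached with an invitation to participate in the study". No exposure group is specified.
- **Community** (Community Selection Details, and Community Selection (if Necessary)): used only if the control quota is not filled. "This involves identifying and recruiting controls from community settings, ensuring a diverse representation". On the sites, "community settings such as local community centers or public spaces will be identified".

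Sampling Methods adds: "Convenience and nonprobability sampling methods will be used for the recruitment of cases and controls". Data Collection: Questionnaire gives the order: "Once cases are identified and interviewed, matching controls will be recruited and interviewed". No matching variable is named. The questionnaire items listed there do not include recruitment source or site, and Data Analysis names no adjustment for either.

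**The concern.** Two of the three sources are specific to one exposure group by design. Because stores approach only users, controls have to come from pedestrians and then, if needed, from community sites. Store-recruited users have no unexposed counterparts from the same place. If store customers differ from passers-by or community-centre visitors in neighbourhood, habits or oral health for reasons other than e-cigarettes, that difference is counted as an e-cigarette effect to the extent that users come from stores.

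This is a different problem from the one the article discloses. Convenience sampling is a general limitation. Drawing the two groups from different places biases the comparison between them, and the article does not name that.

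The stakes are considerable because the group comparison is meant to verify whether e-cigarettes cause lesions, and Research Significance hopes the results will guide legislation. With a planned control proportion of only 2.5%, a small absolute difference in background prevalence becomes a large odds ratio.

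**Working it through.** **The plan's own figure.** Sampling Methods gives 152 per group, 11% against 2.5%, power 80% and P=.04 (read here as the significance level). The two-sided normal approximation at .04 gives power 0.819 and Fisher's exact test 0.789, so the stated power reproduces. The implied odds ratio is (0.11/0.89)/(0.025/0.975) = 4.82. The point below does not depend on this.

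**Who can come from where.**

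| Source | Users | Controls |
|---|---|---|
| Stores | yes | not approached |
| Pedestrians | not excluded | yes |
| Community (contingent) | not sought | yes |

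Only the pedestrian row can hold both groups, and the article does not say how many of each it will supply.

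**Illustration of size.** From the documents: 152 per group, control proportion 2.5%, significance at .05, chi-square or Fisher's exact test. Assumed: no true e-cigarette effect; background prevalence s in store customers of 4%, 5% or 7.5%; 2.5% in everyone recruited elsewhere; a fraction f of users recruited at stores.

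Expected prevalence among users: p = f·s + (1 − f)·0.025.

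Spurious odds ratio: [p/(1 − p)] / [0.025/0.975].

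False-positive rate: the probability, summed over two independent binomial counts of size 152, that the two-sided .05 test rejects (chi-square without continuity correction).

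| s | f | p | Spurious odds ratio | Chi-square rejection |
|---|---|---|---|---|
| 2.5% | any | 2.50% | 1.00 | 4.4% |
| 4% | 1 | 4.00% | 1.62 | 10.3% |
| 5% | 1 | 5.00% | 2.05 | 19.8% |
| 7.5% | 1 | 7.50% | 3.16 | 52.7% |
| 4% | 0.5 | 3.25% | 1.31 | 5.9% |
| 5% | 0.5 | 3.75% | 1.52 | 8.5% |
| 7.5% | 0.5 | 5.00% | 2.05 | 19.8% |

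Example: for s = 7.5% and f = 0.5, p = 0.5 × 0.075 + 0.5 × 0.025 = 0.05, and the odds ratio is (0.05/0.95)/(0.025/0.975) = 2.05.

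**Choice of test.** Data Analysis switches to Fisher's exact test when the chi-square assumptions fail. The expected lesion count per group is 152 × 0.025 = 3.8 at equal prevalence, 152 × 0.0325 = 4.9 for 4% against 2.5%, and 152 × 0.0375 = 5.7 for 5% against 2.5%. Under the usual rule of five, Fisher's test would often apply in the low scenarios. Used throughout with f = 1, it rejects in 1.6% of studies at equal prevalence, and in 5.5%, 12.1% and 41.3% at 4%, 5% and 7.5%.

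**The case against.** The strongest reply is that the separation is incomplete and its extent unknown. Pedestrians are assigned to neither group, and the overview presents store customers and pedestrians together as suited to a study of e-cigarette users, so the street may well supply users too. The community stream is a contingency and includes public spaces. A reader might infer that source and exposure are nearly the same variable, that they hardly overlap, and that the bias therefore cannot be adjusted away. The documents do not show this: if pedestrians supply both groups, there is overlap to work with. That part of the objection stands.

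The size is also open. No figure in the article supports a difference in white-spot prevalence between sites. The top rate of 53% needs the largest assumed difference, every user from a store, and the chi-square test. Under Fisher's test the 4% scenario with all users from stores falls to 5.5%. The illustration is unadjusted, whereas the plan includes multivariable logistic regression and collects occupation, education, income and ethnicity, which could absorb part of a neighbourhood difference. This stands as a limit on the numbers.

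Controls are called matching, and a condensed article may leave the matching variables to a fuller protocol. That is fair, so their absence alone is not the point. But the article does state who is approached at each source, and matching on personal characteristics would not give store-recruited users unexposed counterparts from the same setting.

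Finally, the article acknowledges convenience sampling and the difficulty of participant selection. It does so in general terms, without naming the link between source and exposure or offering a remedy.

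**Conclusion.** The concern holds in a limited form. As written, stores yield only users, the contingent community stream yields only controls, and no common site or time frame, recording of source or adjustment for it is stated. Source is partly tied to exposure, and the primary odds ratio can be biased as a result.

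The size depends on two quantities that the documents do not give: the background difference between store customers and others, and the share of users recruited at stores. Over the assumed range, the spurious odds ratio runs from 1.3 to 3.2 and the chi-square false-positive rate from 6% to 53%, against 4.4% with no difference. With equal background prevalence there is no such bias. These figures show sensitivity; they do not predict the bias.

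A reader might also infer that shared sites would cure the problem. They would not: under Selection of Controls, only controls must have no history of drinking alcohol, and that difference between the groups survives any change of site.

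**What to change.** Keep convenience sampling and the stores, and change the following before enrolment, which has not begun:

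1. Recruit controls as pedestrians around the same stores and in the same high-traffic areas, on the same days and hours and with the same screening questions as for users.
2. If a community top-up is needed, hold it to the same neighbourhoods and screen there for both groups.
3. Record source and site for every participant.
4. Stratify or adjust the odds ratio for site. The planning assumptions imply only about 152 × (0.11 + 0.025) = 20.5 lesions in all, so use a few broad site groups.
5. Report a sensitivity analysis restricted to pedestrian-recruited participants of both groups. It will be less precise, but it is the comparison least affected by source.

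The cost is revised recruiter instructions and the recording of source and site; the sample size is unchanged. The documents give no recruitment costs, so calling this inexpensive is a judgement. The likely downside is slower control recruitment, since eligible non-users who also do not drink may be scarce near e-cigarette stores. The change reduces selection differences and does not remove them.

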#### Community Selection Details

If quotas for controls are not met through the initial recruitment strategy, a community selection approach will be considered. This involves identifying and recruiting controls from community settings, ensuring a diverse representation.

### Clinical Recruitment Procedures

#### e-Cigarette Store Recruitment

The e-cigarette store recruitment consists of 3 stages, which are as follows:

Approach: e-cigarette stores will be approached to seek their cooperation in the recruitment process.Informed consent: store owners and managers will be provided with detailed information about the study objectives, procedures, and ethical considerations. Upon agreement, consent forms may be obtained from the store owners to allow recruitment on their premises.Participant identification: e-cigarette users within the specified age range will be approached, and the study will be explained to them. Interested individuals will be given detailed information about the study and their consent will be sought.

#### Pedestrian Recruitment

The pedestrian recruitment consists of 2 stages, which are as follows:

Approach: pedestrians in high-traffic areas will be approached with an invitation to participate in the study.Informed consent: similar to the e-cigarette store recruitment, detailed information will be provided to potential participants, and consent will be obtained before proceeding with any study-related activities.

#### Community Selection (if Necessary)

If quotas for controls are not met through the initial recruitment strategy, community selection may be considered.

Approach: community settings such as local community centers or public spaces will be identified. Consent from relevant authorities and community leaders will be sought.Participant identification: controls meeting the study criteria will be approached in these settings, and recruitment will follow the same informed consent procedures.

### Sampling Methods

Convenience and nonprobability sampling methods will be used for the recruitment of cases and controls. The detailed sample size determination is shown in Multimedia Appendix 1 [16]. Briefly, the predefined power is 80% (*P*=.04), and the predefined proportions of the case and controlled groups are 11% and 2.5%, respectively. In all, 304 youths aged 15 to 24 years (n=152, 50% who smoke only e-cigarettes and n=152, 50% who do not smoke e-cigarettes or cigarettes) will be recruited.

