**Methods:**

In this prospective study, 304 youths aged 15 to 24 years (n=152, 50% who smoke only e-cigarettes and n=152, 50% who do not smoke e-cigarettes or cigarettes) will be divided into 2 groups for a controlled study. Whether e-cigarettes cause oral mucosal lesions will be verified by comparing the odds of oral mucosal lesions in the 2 experimental groups. For this experiment, the predefined power is 80% (*P*=.04), and the predefined proportions of groups 1 and 2 are 11% and 2.5%, respectively.

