### Data Analysis

Descriptive statistics will be used for all binary, categorical, and continuous variables and expressed as tables, texts, and figures. Bivariate analysis will then be performed for relevant variables. The Shapiro-Wilks test will be performed for continuous variables to determine whether they follow the Gaussian distribution. Afterward, the independent 1-tailed *t* test and 1-way ANOVA will be used; otherwise, the Mann-Whitney *U* test and Kruskal-Wallis test will be performed. For cross-tabulation of 2 categorical variables, the chi-square test will be used. Variables that do not fulfill the assumption of this test will be analyzed using Fisher exact test. Comparisons with *P*=20 will be used to implement multivariable analysis using multiple logistic regression. Odds ratios and 95% CIs will be determined for e-cigarette smoking and other individual factors. For all analyses, *P*<.05 will be used to denote statistical significance. Statistical analyses will be performed using the SPSS (version 27; IBM Corp).

The control and e-cigarette groups will be subjected to a *t* test (assuming the data meet the normality criteria and do not meet the criteria for the rank sum test) to verify whether e-cigarettes cause harm.

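### The article sizes the study at P=.04, tests at P<.05 and makes its only described t test one-tailed, so the significance rule for the main comparison is not settled

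*Protocol article*

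**What the plan says.** The planning level appears in the Abstract (Methods) and in Sampling Methods. The latter says "the predefined power is 80% (*P*=.04", and adds that "the predefined proportions of the case and controlled groups are 11% and 2.5%, respectively". The sample is "n=152, 50% who smoke only e-cigarettes and n=152, 50% who do not smoke e-cigarettes or cigarettes", 304 in total. No direction is stated for the .04. For the derivation the reader is sent elsewhere: "The detailed sample size determination is shown in Multimedia Appendix 1". That appendix is not among the documents at hand.

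The analysis level is in Data Analysis: "For all analyses, *P*<.05 will be used to denote statistical significance". The same section says that, for continuous variables that pass a normality check, "the independent 1-tailed *t* test and 1-way ANOVA will be used". It adds that "For cross-tabulation of 2 categorical variables, the chi-square test will be used", with Fisher's exact test as the fallback, and that odds ratios will carry 95% confidence intervals. None of these other tests is given a direction. Its last paragraph compares the e-cigarette and control groups by a t test, to establish whether e-cigarettes are harmful. No tail is stated there. Under Hypothesis and in the questionnaire section, mucosal health is recorded as white spots present or absent.

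**The concern.** Three rules can be read from the article: .04 (direction unstated), .05 (direction unstated) and .05 one-tailed. They do not always give the same answer on the same data. The only t test the article describes is one-tailed, and the closing comparison is a t test, so a reader may fairly apply the one-tailed rule to the main question. A one-tailed .05 test puts the whole 5% in the harm direction, where a two-sided .05 test puts a nominal 2.5%. It can also call harm significant while the two-sided 95% interval for the odds ratio, reported next to it, includes 1.

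Research Significance says a positive finding would be used to warn users and to guide legislation. The chance of a false declaration of harm should therefore be fixed before any data exist.

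**Working it through.** **Inputs.** From Sampling Methods: p1 = .11, p2 = .025, n = 152 per group, power 80%, level .04. From Data Analysis: level .05 and the one-tailed t test. Assumption: where no direction is stated, I take the test as two-sided.

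**1. The article's sample size.** The pooled-variance formula is

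n = [z(α/2)·√(2p̄(1−p̄)) + z(β)·√(p1(1−p1) + p2(1−p2))]² / (p1−p2)²

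with p̄ = .0675. Then 2p̄(1−p̄) = .12589 (root .3548), p1(1−p1) + p2(1−p2) = .12228 (root .3497), and (p1−p2)² = .007225.

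- Two-sided .04: (2.054×.3548 + .8416×.3497)² / .007225 = 144.8, so 145.
- Two-sided .05: (1.960×.3548 + .8416×.3497)² / .007225 = 135.6, so 136.

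With continuity correction these become 168 and 159. Fisher's exact test by enumeration needs 156 and 148. At two-sided .04, the stated 152 therefore lies inside the range of standard methods (145 to 168).

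**2. Power at 152 per group.** By the pooled approximation, power = Φ[((p1−p2)√n − z·.3548)/.3497], where (p1−p2)√n = .085×12.329 = 1.048. The Fisher column is by exact enumeration.

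| Rule | Pooled approximation | Fisher exact |
|---|---|---|
| two-sided .04 | 81.9% | 78.9% |
| two-sided .05 | 84.3% | 81.5% |
| one-sided .05 | 90.8% | 88.8% |

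Moving from .04 to .05 raises power.

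**3. False declarations of harm.** I enumerated all outcomes for two binomial samples of 152 with the same true rate and summed the probability of significance in the harm direction. At 2.5% in both groups:

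- one-tailed .05: 6.1%
- two-sided .05: 2.2%
- two-sided .04: 1.7%

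The t test on 0/1 data and the two-proportion z test (chi-square without correction) agree to the decimal shown. The ratio of the first two is 6.1/2.2 = 2.8, above the nominal 2 because events are few. At 6.75% in both groups (the average of the two planning rates) the first two are 5.1% and 2.4%.

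**4. Results on which the rules disagree (152 per group).**

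- 11 versus 4: difference 7/152 = .0461. The t test has standard error .0248, t = 1.858 on 302 df, one-tailed P = .032. Chi-square gives z = 1.854, P = .064. The odds ratio is (11×148)/(141×4) = 2.89, with log standard error √(1/11+1/141+1/4+1/148) = .596 and 95% interval 0.90 to 9.28.
- 10 versus 3: chi-square z = 1.984, P = .047, significant at .05 but not at .04.

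Such counts are realistic: 2.5% of 152 is 3.8 events.

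**The case against.** The strongest reply is that the article already fixes one analysis threshold, .05 for everything, and that .04 is only a planning value. The gap between them matters little. By exact enumeration of the chi-square test, P falls between .04 and .05 about 1.0% of the time with 2.5% in both groups (4.43% − 3.44%), and about 1.7% of the time under 11% versus 2.5% (87.0% − 85.3%). The one-tailed wording, moreover, stands in the sentences on continuous variables, while a yes/no outcome would go to chi-square or Fisher. On that reading the 6.1% never applies to white spots.

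The first part stands: .04 against .05 alone is a small inconsistency. The second stands only in part. The closing paragraph assigns the group comparison to a t test, and the article describes no other t test than the one-tailed one. Both readings are open, which is the defect. Whether a t test suits a present/absent outcome is a separate question.

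A reader might also infer that 152 does not follow from the inputs, or that .04 was not the level really used because 136/0.9 = 151.1 rounds up to 152. The documents do not support this. The derivation is in an appendix not shown, 152 lies within the range of standard methods, and 145/0.95 = 152.6, rounded up to 153, would point to .04 just as well. Both allowances are guesses; the article states neither. Nor does the mismatch leave the study short of power, since testing at .05 raises it.

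**Conclusion.** The point holds as a conflict between decision rules. The sizing level differs from the analysis level, and the direction of the main test is open. The larger part is the tail: if the one-tailed rule governs, false declarations of harm at 2.5% in both groups run at about 6.1%, against 2.2% at two-sided .05 and 1.7% at two-sided .04. These figures assume 152 analysed per group, independent participants and a t test or uncorrected chi-square test. Fisher's exact test is more conservative.

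The conclusion does not extend to the sample size or to its adequacy. On the article's own proportions, 152 per group gives 84.3% power at two-sided .05 by the pooled approximation and 81.5% with Fisher. The conflict is visible on the page, and an appendix on sample size could explain the .04 but would not reconcile it with the analysis section. It should be settled before registration and recruitment, neither of which has begun.

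**What to change.** Use one two-sided alpha of .05 throughout.

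- Abstract (Methods) and Sampling Methods: replace the P=.04 by two-sided alpha = .05. State that 152 per group gives about 84% power for 11% versus 2.5% (pooled approximation; about 81.5% with Fisher's exact test).
- Data Analysis: delete the one-tailed qualifier and state that all tests are two-sided. The 95% intervals then match the tests.
- Do not write a 10% allowance, or any other, into the text unless the sample size appendix states it.

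If .04 is truly intended, make it the analysis threshold as well, with two-sided tests. Power at 152 per group is then about 82% (pooled) or 79% (Fisher), and intervals meant to agree with the tests would be 96%.

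The cost is wording only, and N stays at 304. A borderline result that is significant only one-tailed, such as 11 versus 4, would no longer count. No data have been collected, so the change can be made now without looking post hoc.

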Current research on e-cigarettes has solely focused on their ingredients and compared satisfaction levels of e-cigarettes with those of regular cigarettes [8,9]. The safety of e-cigarettes, especially regarding the etiology of oral and maxillofacial diseases or other possible intraoral side effects, is still unclear. Moreover, few studies have reported on the adverse effects of e-cigarette smoking [10]. Recent experiments have only indicated that the use of e-cigarettes could impact the balance in the oral microbiome while allowing for the rapid growth of foreign microorganisms [4]. Nevertheless, many studies recommend that individuals replace cigarettes with e-cigarettes irrespective of concerns about their safety.

Smoking causes damage to the oral mucosa as well as lesions that can lead to the progressive development of oral cancer [11]. According to research, smoking can cause “oral mucosal leukoplakia” and a variety of other oral mucosal diseases. Additionally, it has been shown that leukoplakia is the oral mucosal lesion that is most likely to lead to oral cancer [12]. Most of the white spots on the lips occur on the lower lip, in the junction of the middle, and on the outer third of the lip, which is where people usually hold cigarettes; this can explain the relationship between holding cigarettes and white spots on the lip. White spots are precancerous lesions, and approximately 4% to 7% can develop into oral cancer. According to statistics, 93.1% of patients with oral white spots are smokers [13]. The development of oral mucosal lesions is based on the principle that tobacco irritates the oral mucosa (through cigarette smoke and the chemicals in cigarettes), causing it to react adversely to prolonged irritation. e-Cigarettes operate in a similar way to tobacco, which also irritates the oral mucosa through atomization and chemicals.

The only difference between e-cigarettes and cigarettes is simply that e-cigarettes do not contain tar; both contain many chemicals as well as nicotine. e-Cigarettes tend to have more types of chemicals than cigarettes because of the wide variety of flavors.

Given that it is still unknown whether e-cigarettes influence the development of oral mucosal lesions, the possibility that e-cigarettes can cause damage to the oral mucosa and increase the risk of oral cancer similar to tobacco needs to be studied.

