### Study Design

The adoption of a case-control, prospective, observational study design is motivated by the relatively low incidence of oral mucosal lesions within the general population. This design allows for a focused exploration of the relationship between e-cigarette smoking and oral mucosal health.

Case-control design is particularly suitable for investigating rare outcomes such as oral mucosal lesions, as it efficiently compares individuals with the outcome of interest (cases) to those without (controls).

A prospective design involves following participants over time, allowing for the collection of data on exposures and outcomes as they occur. By prospectively tracking participants, the study can gather real-time information on e-cigarette smoking habits and observe the development of oral mucosal lesions, providing a temporal sequence crucial for establishing causation.

An observational design is chosen over an experimental one due to ethical considerations and the nature of the research question. Since randomly assigning participants to smoke e-cigarettes for an extended period is ethically challenging, an observational approach allows for the examination of naturally occurring exposure to e-cigarette smoking in real-world settings.

The low incidence of oral mucosal lesions in the general population necessitates a design that efficiently targets and investigates this specific outcome. By focusing on a population at risk (e-cigarette smokers) and carefully selecting controls, the study maximizes its ability to detect and understand the potential impact of e-cigarette smoking on oral mucosal health.

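### Multiple logistic regression is planned with only about 3.8 control lesions expected, so the odds ratio is biased away from 1 and may have no finite value; the stated power is not refuted

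*Protocol article*

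**What the plan says.** Sampling Methods gives the planned lesion rates: "the predefined proportions of the case and controlled groups are 11% and 2.5%, respectively". It gives the groups as "n=152, 50% who smoke only e-cigarettes and n=152, 50% who do not smoke e-cigarettes or cigarettes" and says "the predefined power is 80% (*P*=.04". The detailed calculation is in an appendix that is not shown. Selection of Controls admits "individuals without a history of smoking e-cigarettes, drinking alcohol, and smoking tobacco at the time of recruitment". The outcome is the presence or absence of white spots (Hypothesis; Data Collection: Questionnaire).

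Data Analysis screens variables in bivariate tests and carries the selected ones into multiple logistic regression: "Odds ratios and 95% CIs will be determined for e-cigarette smoking and other individual factors". The software is SPSS 27. Fisher's exact test replaces the chi-square test when a cross-tabulation is sparse. No counterpart is given for the regression.

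Two other statements bear on the control rate. Background says "93.1% of patients with oral white spots are smokers", and Study Design justifies the design by "the relatively low incidence of oral mucosal lesions within the general population".

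**The concern.** The odds ratio and its interval are the study's effect estimate, and they come from a model fitted to very few events. The control group is the weak point, because its expected lesion count is in single figures even at the planned rate. Maximum likelihood estimates of a log odds ratio are biased away from zero with so few events. When one group has no events, the estimate is infinite and the usual interval is meaningless.

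The control rate may also be lower than planned. The controls abstain from e-cigarettes, tobacco and alcohol, while the article's own background attributes nearly all white spots to smokers. At stake is whether the main estimate can be reported at all, and whether it is overstated when it can.

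**Working it through.** **Inputs.** 152 per group; 11% and 2.5% (Sampling Methods); significance at 5% (Data Analysis). The .04 in Sampling Methods is read as the significance level used for sizing. Sidedness is not stated there; two-sided is assumed.

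**1. The plan's own power.** Pooled two-proportion formula: z = [Δ√n − z(1−α/2)·√(2p̄q̄)] / √(p1q1 + p0q0), with Δ = 0.085, p̄ = 0.0675, √(2p̄q̄) = 0.3548 and √(p1q1 + p0q0) = 0.3497.
- α = .04: (1.0480 − 2.0537 × 0.3548)/0.3497 = 0.913, power 81.9%.
- α = .05: (1.0480 − 1.9600 × 0.3548)/0.3497 = 1.008, power 84.3%.
- Exact Fisher power: 78.9% at .04 and 81.5% at .05.

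The stated 80% is reproduced.

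**2. Expected lesions.** Controls: 152 × 0.025 = 3.8. Users: 152 × 0.11 = 16.7. Total: 152 × 0.135 = 20.5. The questionnaire's sociodemographic part has six items. With six covariates plus exposure, that is 20.5/7 ≈ 2.9 events per coefficient, and fewer if multi-category items such as ethnicity use several terms.

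**3. Bias at the planned rates.** True odds ratio = (0.11/0.89)/(0.025/0.975) = 4.82. With a lesions in users and b in controls, the log of a(152−b)/[b(152−a)] was averaged over the two binomial distributions, leaving out samples with no finite value, and back-transformed. For Firth's method, which in a 2×2 table adds ½ to each cell, all samples count. The six-covariate row is a simulation of 4,000 data sets with independent normal covariates that have no effect (assumption).

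| Model | Maximum likelihood | Firth |
|---|---|---|
| Exposure only | 5.2 | 4.8 |
| Exposure and six covariates | 5.4 | 4.8 |

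**4. Chance of no finite estimate.** P(no control lesion) = (1 − p0)^152, whatever the rate in users.

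| Control rate | P(no control lesion) |
|---|---|
| 2.5% (planned) | 2% |
| 1.5% | 10% |
| 1.0% | 22% |
| 0.5% | 47% |

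The rates below 2.5% are assumptions chosen to show a range.

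**5. Is a rate below 2.5% plausible?** If 93.1% of people with white spots smoke and a share s of the population smokes, a 2.5% rate in non-smokers implies a rate in smokers of 0.025 × (0.931/0.069) × (1−s)/s = 0.337(1−s)/s. That is 135% (impossible) at s = 20%, 79% at s = 30% and 34% at s = 50%. The value of s is an assumption, because the documents give none. So the figures sit badly together, but the result turns on an unknown.

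**6. What a lower control rate does to power.** With users held at 11%, Fisher power at α = .05 rises to 93% at a control rate of 1.5%, 97% at 1.0% and 99% at 0.5%. Power falls only if the rate in users falls too. With the odds ratio held at 4.82 instead, a 1.0% control rate means about 4.6% in users and power of 48% (chi-square) or 34% (Fisher). A 0.5% control rate means about 2.4% in users and 25% or 8%.

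**The case against.** A reader might infer that the 80% power cannot be reached because 2.5% is too high for abstaining controls. The documents do not support that. The article fixes two proportions and no odds ratio. The value 4.82 is only what those proportions imply. At the stated rates the power is right, and lowering the control rate alone raises it.

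A reader might also infer that the 93.1% figure disproves the 2.5%. It does not. It is the share of smokers among patients with white spots, not a lesion rate in non-smokers. Converting it needs a smoking prevalence, which is not given, and the population behind it may differ from people aged 15 to 24. A rate of 2.5% is itself low, so the Study Design remark does not contradict it either. The source of the 2.5% may be in the appendix.

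Two further objections have some force. First, Fisher's exact test already covers the group comparison: 17 of 152 against 0 of 152 gives P of about 0.00001. That protects the test but not the odds ratio, its interval or the adjusted analysis. Second, the choice of fitting method is often left to an analysis plan. Here, though, the article names the model and the software and supplies a sparse-data fallback for tables only. The bias in step 3 arises at the plan's own rates, so it does not depend on any assumed lower rate.

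**Conclusion.** The point holds as one about estimation. At 11% and 2.5% with 152 per group, ordinary maximum likelihood overstates a true odds ratio of 4.82 as about 5.2 to 5.4 on average, and in 2% of studies gives no finite value. The second figure rises to 22% at a control rate of 1.0% and 47% at 0.5%. The upper end of the bias range rests on six covariates without effect; the lower end needs no covariate assumption.

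That the control rate is below 2.5% is plausible but not shown. The stated power stands, conditional on the two absolute rates, and would be lost only if the rate in users also fell well below 11%. The matter should be fixed before recruitment, which has not begun.

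**What to change.** In Data Analysis, fit the multivariable model by Firth-penalised (or exact) logistic regression in place of ordinary maximum likelihood. With Firth's method, take the 95% confidence intervals from the profile penalised likelihood. The odds ratio remains the effect measure, as planned.

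In Sampling Methods, and in the matching sentence of the Abstract, state that the 80% power is conditional on absolute rates of 11% in users and 2.5% in controls who use no e-cigarettes, tobacco or alcohol.

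The cost is a few sentences and possibly an add-on or software other than the standard SPSS logistic procedure. No more participants are needed. Penalisation keeps the estimate finite but cannot create information: with an empty control cell the interval will still be very wide.
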